### Study design

This article was written in accordance with the Standard Protocol Items: Recommendations for Interventional Trials (SPIRIT) checklist (Additional file 2). The effects of the program on registration behaviour, registration intention and beliefs regarding organ donation and registration will be evaluated in a CRCT with post-test only (see Figs. 1 and 2). The program will be offered to both the control and experimental groups. Students in the control group will complete the evaluation questionnaire before receiving the program, while the experimental group will do this after receiving the program. Differential attrition can be prevented, as all participating classes will receive the program. A post-test design prevents the risk of testing bias by priming students for the program by filling out the questionnaire beforehand [22]. The absence of a pre-test, however, might also threaten internal validity, since equivalence of the groups cannot be established. The threat of possible differences at baseline will be minimized by using a large number of randomization units and a proper randomization [23].

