### Procedure

The educational program will be provided by the teachers in IVE schools during regular classes. They will receive a link via e-mail prior to the start of the study. With this link, both teachers and students can reach the website. Before the first lesson, the control group will complete the effect evaluation questionnaire. All participants will then receive lesson 1, with the video fragments and group discussions. During the next session, they will both receive lesson 2a, the quizzes with tailored feedback, and lesson 2b, the exercise on completing an organ donation registration form. Teachers will have the freedom to provide the lessons whenever it fits their schedule, but we expect that in most cases lesson 2 will be delivered within 1 or 2 weeks after lesson 1. After the whole program is delivered, students in the experimental group will fill in the evaluation questionnaire. Six months after the implementation of the program, participating students (students from both the experimental and control groups) will receive a follow-up questionnaire during class to measure their registration behaviour. New control classes will then be recruited to compare the registration behaviour of students who received the program with that of students who did not. Data for the process evaluation will be gathered partly during the program delivery and partly after. During the program delivery, data will be collected on usage (e.g. by means of Google Analytics), while after the program delivery, reasons for particular usage behaviour will be assessed (e.g. by means of interviews). Moreover, students in the experimental groups will complete a process evaluation questionnaire after the program is delivered.

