### Statistical analyses

The first aim of this study is to investigate the effectiveness of the educational program on the intention to register a choice (i.e. the primary outcome in the study at hand, measured as yes or no). All data for the effectiveness are gathered from questionnaire E. Secondary outcomes will be the choice students intend to make (yes or no donation), behavioural determinants and finally their actual registration behaviour 6 months after receiving the intervention. The differences in outcomes between the intervention and the control group will be analysed using multilevel regression models, taking into account that students are nested within classes which in turn are nested within schools. Besides intervention group, several demographic characteristics are included in these models (i.e. sex, study discipline, age, religion and educational level), as they are expected to be associated with the outcomes.

As a post-test only design was used, there are no missing data in terms of participants dropping out in between measurements. Therefore, when comparing the experimental and control groups, missing data will not be an issue—we have all data from participants who agreed to participate. The mixed model analysis is then valid under the assumption of missing at random (MAR). However, when correcting for covariates, missing could become an issue, as participants can skip items in the questionnaire. This will be dealt with using multiple imputation (MI).

The second aim is to analyse the implementation of the program. Interviews will be audio-recorded, and a transcript will be written from each interview. The transcripts will be marked with labels using open coding. These codes will be categorized (selective coding), resulting in matrices in which facilitators and barriers of the implementation will be identified. Quantitative data from Google Analytics, the teachers’ logbooks and students’ questionnaires (questionnaire P) will be used for descriptive analyses to provide insight into how the program was used, delivered and received.

All data will be stored on a secured service and will only be accessible by the study team. A data entry check will be performed on the data from the questionnaires; range checks will also be performed. The interviews will be coded independently by two researchers.

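### The plan says differential attrition is prevented and missing data are no issue, yet its own schedule lets loss during the program remove primary outcomes in the experimental arm only

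*Protocol article*

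**What the plan says.** Two statements dismiss loss of data.

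- Study design: "Differential attrition can be prevented, as all participating classes will receive the program".
- Statistical analyses: because the design is post-test only, "there are no missing data in terms of participants dropping out in between measurements". It continues: "Therefore, when comparing the experimental and control groups, missing data will not be an issue", on the ground that "we have all data from participants who agreed to participate". The next sentence rests the mixed model on a missing-at-random (MAR) assumption. Multiple imputation is then brought in for the covariate-adjusted models, because "participants can skip items in the questionnaire".

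The Procedure section sets the timing of the primary outcome (intention to register, from questionnaire E).

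- Control arm: "Before the first lesson, the control group will complete the effect evaluation questionnaire".
- Experimental arm: "After the whole program is delivered, students in the experimental group will fill in the evaluation questionnaire".
- Interval: teachers choose the dates, and "we expect that in most cases lesson 2 will be delivered within 1 or 2 weeks after lesson 1".

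Questionnaire F follows about six months later and supplies the secondary outcome of self-reported registration. Under Ethical approval, participation is voluntary and consent can be withdrawn at any time.

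**The concern.** Both statements argue from the wrong interval. Attrition that matters to a randomised comparison runs from randomisation of the class to measurement of the outcome, not from one measurement to the next. A post-test-only design has no gap between measurements for questionnaire E, but it still has this one, and the gap differs by arm. Experimental classes must get through two lessons before the primary outcome exists; control classes need none. Giving controls the program after they have been measured does nothing to equalise loss before measurement.

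If the experimental students lost in that period differ in intention from those who stay, the arms are no longer comparable, and a difference can appear without any program effect. The plan declares the risk absent, and so gives no reason to count or examine it. The possible pitfalls listed in the Discussion do not include it either.

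**Working it through.** **Setting the sections side by side**

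| Step | Control class | Experimental class |
|---|---|---|
| Randomised | yes | yes |
| Must pass before questionnaire E | nothing from the program | lesson 1, a gap usually of 1 to 2 weeks, lesson 2 |
| Loss possible on questionnaire day | yes | yes |
| Loss possible during the program, before the outcome | no | yes |

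The last row contradicts the two statements. Questionnaire F is a second measurement, so the premise of no dropout between measurements also fails for the six-month outcome.

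**What the model does.** Each student has one intention outcome. A mixed model fitted to students with questionnaire E is therefore a complete-case analysis. It is valid if loss is unrelated to intention given the modelled covariates (sex, discipline, age, religion, level). A student with no questionnaire E supplies neither outcome nor questionnaire covariates.

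**The plan's own sample size.** 16.2 × 0.738 = 11.96, so 12 unregistered students per class; 12 schools × 1.15 = 13.8, so 14; 14 × 10 × 12 = 1680, or 840 per arm. This reproduces the stated total. The 15% is for variation in class size, so there is no allowance for loss. The power of 0.839 cannot be checked directly, because no control rate is given.

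**Illustration under no true effect**

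Inputs from the plan: α = 0.05 two-sided, class ICC 0.02, 12 students per class, a 20% relative increase as the target.

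Inputs assumed:
- Intention p = 0.427 in both arms. This is close to 0.428, the control rate at which 720 per arm, a 20% relative increase and a design effect of 1.22 give the plan's 0.839.
- A share m of experimental students is lost in excess of controls, and their intention is q.

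Formulas:
- Design effect = 1 + (12 − 1) × 0.02 = 1.22, so effective n = 840/1.22 = 688.5 in control and 688.5(1 − m) in experimental.
- Observed experimental intention = (p − m·q)/(1 − m).
- Type I error = 1 − Φ(1.96 − d/SE) + Φ(−1.96 − d/SE), where d is the spurious difference.

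Worked case, m = 0.15 and q = 0.30:
- Observed intention = (0.427 − 0.045)/0.85 = 0.4494, so d = 0.0224.
- SE = √(0.427 × 0.573/688.5 + 0.4494 × 0.5506/585.2) = 0.0279, so d/SE = 0.80.
- Type I error = 0.127.

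| Lost (m) | Intention of lost (q) | Observed | Difference | Type I error, 840 per arm | 720 per arm |
|---|---|---|---|---|---|
| 10% or 15% | 42.7% | 42.7% | 0 | 0.050 | 0.050 |
| 5% | 30% | 43.4% | +0.7 points | 0.057 | 0.056 |
| 15% | 30% | 44.9% | +2.2 points | 0.127 | 0.115 |
| 10% | 20% | 45.2% | +2.5 points | 0.151 | 0.136 |
| 15% | 55% | 40.5% | −2.2 points | 0.123 | 0.112 |

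The 720 column is the design before the 15% increase. At p = 0.427 a 20% relative increase is 8.5 points, so +2.2 and +2.5 points are 26% and 30% of it. That 8.5 follows from the assumed rate and is not a figure in the plan. The last row shows that the sign of the bias depends on who is lost.

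**The case against.** The case on the other side is substantial, and most of it stands as a limit on how far the point goes.

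- **Loss is possible, not shown.** A reader might infer that loss does occur, and only in the experimental arm. The documents give no loss rate for either arm, and controls can also be absent, decline or withdraw. Only loss during the program period is specific to one arm.
- **It is not completers against all controls.** The Procedure section ties questionnaire E to delivery of the program to the class. It does not require a student to have attended both lessons, and only controls who are present and consent are measured.
- **The direction is open.** A reader might infer bias in the program's favour. That needs the lost students to have lower intention. In addition, only unregistered students answer the intention item, so experimental students who register during the program leave the denominator. With assumed true rates of 40% and 48%, 5% registering gives (0.48 − 0.05)/0.95 = 45.3% observed, which pulls the other way.
- **Some information will exist.** Logbooks record the components delivered, and Google Analytics shows class-level use and quitting. Non-delivery would be visible by class, although the article does not link these data to the primary analysis.
- **Imputation is not limited to covariates in so many words.** The text introduces it for the adjusted models because items can be skipped. Whether a skipped intention item is covered is unclear, not excluded.
- **Details may sit in a fuller plan.** Response tables and imputation models are commonly left there, so their absence is not the point.

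None of this rescues the two statements. They are positive claims, and the schedule in the same article contradicts them. The section also says that missing data are no issue and then relies on MAR.

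**Conclusion.** The point holds in a limited form. The claims that differential attrition is prevented and that missing data will not affect the arm comparison are wrong as written. Loss during the program can precede the primary outcome in the experimental arm only, and non-response to questionnaire F is loss between measurements.

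The size and direction of any bias are unknown. Loss unrelated to intention costs precision only. Under the assumed 42.7% intention, the two scenarios with lower intention among the lost give +2.2 and +2.5 points and a type I error between 0.115 and 0.151; the smaller 5% loss barely matters. These figures show that moderate selective loss would be enough to count. They do not predict what will happen in this trial, and the documents do not support saying that the primary result is biased. Severity: should-fix.

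**What to change.** 1. Withdraw both statements. Say instead that loss before questionnaire E can differ by arm, and that questionnaire F can be missed.
2. Take the class list at randomisation as the denominator. Report completion of questionnaires E and F by arm, at class and student level. Count all listed students, because registration status is unknown for those who return nothing. Counts are enough, so anonymity is kept.
3. Analyse all randomised classes and all available students by assigned arm, whatever was delivered or attended.
4. State that multiple imputation also covers skipped intention items.
5. Add a sensitivity analysis that does not assume MAR for experimental students without questionnaire E, varying their assumed intention below and above that of respondents.
6. Treat non-response to questionnaire F as missing data.

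The cost is a count per class, some additional analysis and a possibly less favourable estimate. Trial status says recruitment of classes was completed in June 2018, so lists may have to be obtained from schools after the fact. Moving questionnaire E to a fixed date is not proposed: it would conflict with the scheduling freedom given to teachers and may come too late.

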## Discussion

This protocol describes a study to evaluate both the effectiveness and implementation of a program aimed at encouraging lower-educated adolescents to make a well-informed decision about organ donation and to register this choice. The study is strong in combining several methods and a variety of data sources. The data triangulation serves two main goals: confirmation of findings and completeness [29]. The combination of qualitative and quantitative methods is valuable, as both methods separately will not be sufficient [21]. By combining the methods, flaws can be neutralized and benefits can be strengthened [30]. This leads to a higher validity of conclusions.

There are also possible pitfalls of the study. However, by acknowledging them beforehand and taking them into account during the execution, risks can be limited. A threat during the execution of the program is the possibility of contamination. If students in the experimental group receive the program before students in the control group, students in the control group could hear about the content, biasing their answers on the evaluation questionnaire. Ideally, students from both groups (within one school) will receive the program simultaneously. However, in many cases, we expect this to be difficult due to organizational reasons and because often these classes are being taught by the same teacher. If students in the control group hear about the content before filling in the baseline questionnaire, this could influence their answers in the direction of expected intervention effects and therefore most probably lead to an underestimation of the program effect in the end.

Finally, the effectiveness of the program in terms of registration behaviour is difficult to measure. As official organ donation registration records are private, no objective data can be gathered regarding the actual registration numbers of participants. The intention to register will be measured directly after receiving the program. To gain some insight into the registration behaviour, participants will be asked about their registration status 6 months after receiving the program. The registration behaviour will thus be based on self-reported registration status. This is, however, the best possible option concerning the circumstances.

The findings of the study can help further improve the program and function as a guideline for a solid dissemination plan. Results from the process evaluation will show how the program was implemented and how this can be improved in the future. The interviews with teachers give further details on circumstances that should be taken into account when disseminating the program to a larger scale. Moreover, the study will provide insight into the translation of research into practice of school-based health promotion interventions, which can serve as an example for others.

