**Fig. 2 Fig2:**
[figure not shown]
SPIRIT figure

After agreement to participate, classes will be matched by members of the study team to improve the equivalence of the groups. The classes will be matched on study discipline, and matched classes will be from the same school. From each pair of matched classes, one class will be randomly assigned to the experimental condition, while the other class will then be assigned to the control condition. Teachers will be notified as to whether they have to hand out the questionnaire before or after delivering the program to students.

The implementation of the educational program will be evaluated using both qualitative (i.e. semi-structured interviews) and quantitative (i.e. logbooks, questionnaires, Google Analytics data) methods, both during and post-delivery.

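### No order is set between the control classes' questionnaire E and experimental lessons in the same school, so a contamination bias the protocol itself concedes is left open

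*Protocol article*

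**What the plan says.** Randomization is by class within matched pairs, and "matched classes will be from the same school" (protocol article, Study design). Both arms receive the program; the arms differ in when questionnaire E is completed.

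For control classes the Procedure section says: "Before the first lesson, the control group will complete the effect evaluation questionnaire". The reference point is that class's own first lesson. The same section leaves dates open: "Teachers will have the freedom to provide the lessons whenever it fits their schedule". The instruction described under Study design concerns only the order within a class: "Teachers will be notified as to whether they have to hand out the questionnaire before or after delivering the program to students".

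The Discussion names the threat when the experimental class goes first: "students in the control group could hear about the content, biasing their answers on the evaluation questionnaire". It continues: "Ideally, students from both groups (within one school) will receive the program simultaneously". It then says that in many cases "we expect this to be difficult due to organizational reasons and because often these classes are being taught by the same teacher", and concludes that such leakage would "most probably lead to an underestimation of the program effect in the end".

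The Google Analytics section adds that class-level website data allow a check on whether the two classes of a pair had the program at about the same time. No rule on order follows, and no use of that check in the analysis is described.

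**The concern.** Simultaneous delivery is sufficient to protect the control answers but not necessary. The control outcome is one questionnaire completed without any teaching, so its date can be separated from the lessons. What matters is that control E comes before experimental students in the same school have anything to pass on. A shared teacher, which the protocol gives as an obstacle to simultaneity, does not prevent that order.

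At stake are the outcomes taken from E in both arms: intention to register (primary), the intended choice and the behavioural determinants. Leakage moves control answers toward the experimental arm, so the estimated effect shrinks and power falls. The sample size section makes no allowance for this. Its 15% increase in schools is assigned to varying class size.

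**Working it through.** **1. The texts side by side.**

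| Question | What the article fixes |
|---|---|
| When is control E completed? | Before that class's own lesson 1 (Procedure) |
| When are lessons given? | At the teacher's choice (Procedure) |
| Is there an order between classes in a school? | None stated |
| Can the order be checked? | Partly and afterwards, from class-level website dates (Google Analytics) |

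A control class can therefore follow every instruction and still complete E after its matched class has finished the program.

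**2. Inputs.** From the sample size section: two-sided alpha 0.05, target power 80%, relative increase 20%, ICC 0.02 (class) and 0.01 (school), 12 unregistered students per class, 10 classes per school. Twelve schools give 12 × 10 × 12 = 1440 students, 720 per arm, with stated power 0.839. Fourteen schools give 1680, 840 per arm. Assumed here: control rate 0.43, hence experimental rate 1.2 × 0.43 = 0.516, and a contamination share c, the average fraction of the program effect that control students take on.

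**3. The stated power.** It came from simulation and the control rate is not given, so 0.839 cannot be reproduced independently. As an approximation, classes are randomized within schools, so the school component cancels and the design effect is (1 − 0.02 − 0.01) + 12 × 0.02 = 1.21. Then:

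- effective n per arm = 720 / 1.21 = 595
- SE = √[(0.43 × 0.57 + 0.516 × 0.484) / 595] = 0.0288
- power = Φ(0.086 / 0.0288 − 1.96) = 0.85

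This is close to 0.839 because 0.43 was chosen to be roughly the rate that returns it. It calibrates the illustration and does not confirm the rate. Other design effects, from 1 (no clustering) to 2.41 (as if schools were randomized), would imply control rates from 0.38 to 0.58.

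**4. Effect of contamination.** Control rate = 0.43 + c × 0.086; observed difference = (1 − c) × 0.086.

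| c | Control rate | Difference (points) | Power, 12 schools | Power, 14 schools |
|---|---|---|---|---|
| 0 | 0.430 | 8.6 | 0.85 | 0.90 |
| 10% | 0.439 | 7.7 | 0.76 | 0.83 |
| 20% | 0.447 | 6.9 | 0.66 | 0.73 |
| 30% | 0.456 | 6.0 | 0.55 | 0.61 |

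The 14-school column treats the increase for varying class size as if it were spare, so it is the more favourable one.

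**5. Sensitivity.** If the control rate is re-solved under each design effect so that power without contamination is 0.839 at 12 schools, 10% contamination gives about 0.76 (12 schools) and 0.82 (14 schools), and 20% gives 0.65–0.66 and 0.72–0.73. The loss depends on c far more than on the assumed rate. Whatever the rate, the required sample grows by roughly 1/(1 − c)²: 1.23 at 10% and 1.56 at 20%.

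**6. Reading c.** Only pairs in which the experimental class started before control E can be affected. If half the pairs were, an average c of 10% would need 20% transfer within those pairs, and 20% would need 40%.

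**The case against.** The protocol discloses the limitation, gives its likely direction and says that risks can be contained during execution. Four arguments against the point deserve an answer.

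- **The text does not say that experimental classes will go first.** Correct. A reader might infer that they usually will, or that the protocol calls contamination unavoidable. The Discussion says neither. It expects simultaneity to be difficult, and non-simultaneous delivery includes the control-first order, which does no harm to E. The frequency of the harmful order is unknown.
- **A timing check exists, and a sensitivity analysis may be in the analysis plan.** Both are fair, and the absence of a sensitivity analysis from the article is not counted as a fault. But the check comes after the fact, concerns program dates rather than the date of E, and prevents nothing.
- **The remedy has its own bias.** If all control classes completed E first and experimental dates then stayed free, arm would become tied to calendar time. Under simultaneous delivery the gap between arms is about one program length, with lesson 2 expected a week or two after lesson 1; under a loose rule it has no upper limit. These students are around the age of the ministry's registration letter, so a long gap could matter in either direction. This stands, and it is why the order needs a short interval attached.
- **The rule would not remove all leakage.** A reader might infer that it would. Control students can still talk about the questionnaire to experimental students, and a shared teacher will already have handled it. The rule blocks lesson content from reaching control answers, which is the larger channel and the one the protocol names.

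The power illustration also rests on assumed values. At 10% with 14 schools it stays above the 80% target, and the sample size section holds matching back as uncounted reserve.

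**Conclusion.** The point holds as a design weakness. The protocol concedes a probable bias toward the null in its primary outcome, considers one remedy that it expects to be hard to achieve, and sets no order between control E and experimental lessons, although control E depends on no lesson. This conclusion rests on the text and not on the power figures.

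The size is illustrative only: with a control rate of 0.43, power falls from about 0.90 to 0.83 and 0.73 (14 schools), or from about 0.85 to 0.76 and 0.66 (12 schools), at 10% and 20% average contamination. The documents give neither input, so they do not support a claim that the trial is underpowered. Nor do they support a concern about a false positive: the expected harm is an underestimated effect and lost power. The six-month registration comparison is outside this point, because it uses newly recruited control classes.

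**What to change.** **For classes still to be taught.** Instruct teachers that control classes complete E before the experimental classes in the same school start lesson 1; at minimum this covers the matched class and any class with the same teacher. The experimental class should start soon afterwards so that the calendar gap between arms stays short. Record the date of E for every class.

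**For classes already run.** Recruitment of classes closed in June 2018, so this may be many of them. Use class-level website dates and any recorded E dates to flag pairs in which the experimental class started before control E, then repeat the primary analysis without those whole pairs. Dropping whole pairs keeps the matching intact, but class order arises after randomization, so this should remain a sensitivity analysis. Logbooks should not be relied on for dates: the Logbooks section lists components delivered, time spent, satisfaction and comments only.

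**Cost.** A separate short slot in control classes, some scheduling work within each school, and a somewhat earlier control measurement. Allocation, outcome and sample size do not change. Leakage would be greatly reduced, not eliminated.
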